### Statistical Analysis

All statistical analysis will be performed with the software at URC et CIC Paris Descartes Necker-Cochin. A Statistical Analysis Plan (SAP) will be written and finalized before study closure, i.e., database closure. The SAP will provide full details of the analyses and data displays.

Descriptive statistics will be presented for each treatment with mean, median, SD, standard error, quartiles, minimum, maximum, and the two-sided 95% confidence limits of mean and median. Frequency tables will be presented where applicable. All statistical tests will be two-sided with an alpha level set to 0.05 and will be adjusted on the stratification variables used for randomization.

The main analysis of the primary efficacy endpoint will be performed on the intention-to-treat population. The superiority analysis will be performed by a χ^2^ test (or by a Fisher's exact test if any expected number was <5) considering the percentage of patients presenting 90-day = grade B or C postoperative pancreatic fistula as defined by the ISGPF. It will be planned to adjust the analysis on the stratification variables (i.e., the type of procedure and the presence or absence of main pancreatic duct dilatation) using a multivariate logistic regression.

The secondary analyses will be performed on the intention-to-treat and per-protocol populations. The 60-day grade 3 pancreatic complication rate (fistula, leak, and abscess), the 90-day overall pancreatic fistula rate (grades A, B, and C), the 90-day overall complication rate (grades 1–5) as well as the severe complication rate (grades 3–5), mortality (grade 5), and readmission rate will be compared between patients who receive perioperative somatostatin and octreotide by χ^2^ tests (or Fisher's exact tests if any expected number was <5).

Secondly, these analyses will be adjusted on the type of procedure and the presence or absence of main pancreatic duct dilatation using multivariate logistic regressions. The overall duration of drainage required in patients who develop pancreatic complications and the overall length of stay will be compared between patients who receive perioperative somatostatin and octeotride using Student's *t* tests (or Wilcoxon rank tests if non-normally distributed).

Multivariate linear regressions will be then performed to adjust these analyses on the stratification variables (data transformation could be done in case of non-normal distribution). Additional analyses could be provided according to different subgroups, i.e., based on the stratification variables (i.e., the type of procedure and the presence or absence of main pancreatic duct dilatation) or on the placement or non-placement of a drain at the time of surgery. In addition, sensitivity analyses could be provided to explore different hypothesis regarding the handling of lost to follow-up patients.

A cost-effectiveness analysis will be performed as a secondary endpoint. The aim of the economic evaluation is to assess the cost-effectiveness of continuous intravenous infusion of somatostatin vs. subcutaneous octreotide in patients undergoing either pancreaticoduodenectomy or distal pancreatectomy. Our methodology follows the French and CHEERS guidelines [(15) #1172]. Effectiveness values will be derived from the clinical endpoints. We propose to use two effectiveness endpoints based on the trial's objectives:

The percent of patients with grade B or C postoperative pancreatic fistula at 90 days.90-day severe complication rate (grade 3–5) and mortality.

We will compute and incremental cost per adverse outcome averted and an incremental cost per survivor. Baseline results will be presented as mean ± SD, median interquartile ranges (IQR), or as frequencies with percentages. Resource use data will be presented as means with standard error of the mean despite non-normal distribution because they better represent per patient data than median values and compared using non-parametric testing. Costs, life-years, and complications will be presented as means with 2.5–97.5% bootstrapped intervals. Between-group comparisons of costs will be performed using the bootstrap *t*-test. Between-group comparisons of effects will be performed using non-parametric testing.

The non-parametric bootstrap resampling technique will be used to test the sensitivity of the calculated incremental cost-effectiveness ratios and plot cost–acceptability curves to demonstrate different threshold values for a complication averted. This would show the probability that somatostatin is the preferred treatment option over octreotide at different values for the decision-maker's willingness to pay for a complication or death averted. If patients in the somatostatin group have better health outcomes and lower costs because of reduced hospital stays, somatostatin may prove to be a dominant strategy. Should the incremental cost-effectiveness ratio prove acceptable, a budget impact analysis will be performed to estimate the additional cost to replace octreotide by somatostatin in patients undergoing pancreaticoduodenectomy or distal pancreatectomy (roughly 6,000 patients yearly in France).

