### Randomization

Patients are 1:1 randomized in two groups, in the operating room just after skin incision and surgical exploration to exclude patients with carcinomatosis and metastasis, using permutated blocks of random size to stratify group assignment according to the type of procedure (PD or DP) and the presence or absence of main pancreatic duct dilatation (defined as main-duct diameter of >4 mm at the site of pancreatic transection on preoperative imaging). The randomization list is established centrally by the statistician of the URC et CIC Paris Descartes Necker Cochin before the start of the trial. The document describing the randomization specifications and the randomization list are kept confidentially in a secured place URC et CIC Paris Descartes Necker Cochin. The randomization list is implemented in a randomization tool of the e-CRF on Cleanweb software by the URC et CIC Paris Descartes Necker Cochin. Only the statistician and the person implementing the list in the e-CRF have access to the list during the trial. Randomization is performed by the site staff using the centralized tool in the e-CRF just after skin incision and surgical exploration to exclude patients with carcinomatosis and metastasis.

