### Sample Size Considerations

In daily surgical practice, pancreaticoduodenectomy represents about 80% of pancreatic resection. According to the last two randomized controlled studies performed in France within the FRENCH network, we can estimate the overall rate of grade B/C pancreatic fistula to be about 30% (Table 4). We hypothesize that the use of somatostatin can decrease this rate to 20%. To detect this difference, with an alpha risk of 5% and a power of 80%, a sample size of 294 eligible patients per arm is necessary. Assuming that approximately between 10 and 20% of the patients will not be resected for clinical reasons, a total of 654 patients should be included. These 654 patients will constitute the primary analysis population.

**Table 4 T4:** Reported rate of pancreatic fistula in recent French studies.

		**Type of surgery**	***n***	**% fistula**	
				**A/B/C**	**B/C**
Pessaux et al. (4)	Randomized controlled trial	Pancreaticoduodenectomy	158	34.2	30.3
Sa Cunha et al. (5)	Randomized controlled trial	Distal pancreatectomy	270	55.6	27.3

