## Discussion

Mortality rates after pancreatectomy have decreased to ~2–4% at high-volume centers; however, morbidity after those pancreatic surgeries has remained over the last 30 years between 30 and 50% (16–19). The postoperative morbidity is mainly explained by pancreatic fistula, hemorrhage, and delayed gastric emptying. PF, leak, and abscess area group of complications related to the anastomosis (PD) or closure (DP) of the pancreatic remnant. Pancreatic complications are known to be secondary to the leakage of pancreatic exocrine secretions and/or enteric contents and have been reported in 20–50% of patients who undergo pancreatic resection (1–5). Previous studies have investigated patients and tumor factors associated with the risk of developing postoperative pancreatic fistula, leak, and abscess (1, 20–23). The factor most frequently associated with a decreased risk of these complications is the presence of a dilated pancreatic duct. In addition, tumor location (head/neck vs. body/tail) and the type of resection (pancreaticoduodenectomy vs. distal pancreatectomy) has been reported to be associated with the frequency and severity of pancreatic fistula, leak, and abscess (24). As pancreatic duct size and tumor location cannot be modified, many investigators have evaluated operative and postoperative techniques for reducing the prevalence of postoperative fistula, leak, and abscess after pancreatectomy (25).

Several prospective randomized studies have found pancreaticogastrostomy to be equivalent or only minimally superior to pancreaticojejunostomy with respect to the occurrence of postoperative fistula and leak, and both appear superior to pancreatic duct obliteration without anastomosis (26–28). External drainage of pancreatic duct with a stent seems to reduce leakage rate of pancreaticojejunostomy after pancreaticoduodenectomy, but remain infrequently used (4, 29) and is useless after distal pancreatectomy. In patients undergoing distal pancreatectomy, a variety of techniques for remnant closure have been reported (hand-sewn, stapled, stapled with pledget reinforcement) without clear advantage for any specific technique (30).

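### The protocol says every test is adjusted for the randomisation strata, yet names an unadjusted chi-square for superiority and leaves the adjusted model unlabelled; one stratum-adjusted primary test should be named

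*Protocol article*

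**What the plan says.** All references are to the protocol article.

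- Statistical Analysis, general rule: "All statistical tests will be two-sided with an alpha level set to 0.05 and will be adjusted on the stratification variables used for randomization".
- Statistical Analysis, primary endpoint: "The superiority analysis will be performed by a χ^2^ test", with Fisher's exact test if an expected count is below 5. The quantity compared is the percentage of patients with grade B or C fistula by 90 days.
- Same paragraph, immediately afterwards: "It will be planned to adjust the analysis on the stratification variables", by logistic regression on procedure and duct dilatation. No label says whether this model decides superiority or supports it.
- Statistical Analysis, binary secondary endpoints: chi-square or Fisher first, and then "Secondly, these analyses will be adjusted on the type of procedure and the presence or absence of main pancreatic duct dilatation".
- Randomization: allocation is 1:1, in permuted blocks of random size, stratified by procedure (PD or DP) and by main duct above 4 mm or not.
- Discussion: "The factor most frequently associated with a decreased risk of these complications is the presence of a dilated pancreatic duct".
- Sample Size Considerations: 30% versus 20%, alpha 5%, power 80%, 294 per arm, 654 in total.

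**The concern.** A chi-square test on the pooled two-by-two table is not adjusted for anything. If it is the superiority test, the rule that all tests are adjusted is false for the most important test in the trial. If the rule governs, the named superiority test is the wrong one. The logistic model would satisfy the rule, but its standing is not given.

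Two things are at stake. The first is clarity: a confirmatory phase III trial should have one identifiable p-value for its only powered endpoint. It should also have one effect measure, and these two analyses lead to different ones. The chi-square compares percentages, while the logistic model yields an odds ratio conditional on the strata.

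The second is efficiency. Stratified allocation balances the arms on a prognostic factor, so the difference in proportions varies less than the pooled chi-square variance assumes. A test that ignores the strata forgoes that gain.

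**Working it through.** **1. The plan's own figure.** With p1 = 0.30, p2 = 0.20 and mean 0.25, the pooled-variance formula for an unadjusted comparison is

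n = [1.960·√(2·0.25·0.75) + 0.842·√(0.30·0.70 + 0.20·0.80)]² / 0.10²
= [1.960·0.6124 + 0.842·0.6083]² / 0.01 ≈ 293.2, rounded up to **294 per arm**.

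Then 2·294 / 0.90 = 653.3, rounded up to **654**. Both reproduce, and power at 294 per arm is 80.1%. The sample size is therefore that of the unadjusted test.

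**2. Inputs for comparing the tests.**
- From the document: 588 evaluable patients, 1:1 allocation, 80% PD, overall rates 30% and 20%.
- From Table 4 of the document: DP versus PD odds ratio (0.273/0.727)/(0.303/0.697) ≈ 0.86.
- Assumed, because the document gives neither: share with a dilated duct (30% or 50%) and the odds ratio of fistula for a dilated duct (1 to 0.1).
- Allocation is taken as balanced within the four strata.

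**3. Why the chi-square is conservative.** Take 50% dilated ducts and a duct odds ratio of 0.2. The control risks that average 30% are 0.464 and 0.147 (PD, not dilated and dilated) and 0.426 and 0.129 (DP), with weights 0.4, 0.4, 0.1 and 0.1.
- Within-stratum variance: 0.4·0.464·0.536 + 0.4·0.147·0.853 + 0.1·0.426·0.574 + 0.1·0.129·0.871 ≈ 0.185.
- Variance used by the chi-square: 0.30·0.70 = 0.210.
- Ratio ≈ 0.88, square root ≈ 0.94. The effective critical value is 1.96/0.94 ≈ 2.09, and the two-sided type I error is about 3.7%, not 5%.

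**4. Simulation.** 20,000 trials under the alternative and 40,000 under the null, chi-square versus adjusted logistic regression (Wald test). Cochran-Mantel-Haenszel gave almost the same results as the logistic model.

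| Dilated | Duct odds ratio | Type I error, chi-square / adjusted | Power, chi-square / adjusted | Gain in points |
|---|---|---|---|---|
| 30% | 1 | 4.9% / 4.9% | 80.6% / 80.6% | 0 |
| 30% | 0.5 | 4.8% / 5.0% | 80.5% / 80.8% | 0.4 |
| 30% | 0.3 | 4.5% / 5.1% | 81.1% / 82.3% | 1.1 |
| 30% | 0.2 | 4.2% / 5.0% | 81.1% / 82.7% | 1.6 |
| 50% | 1 | 5.2% / 5.2% | 80.5% / 80.4% | 0 |
| 50% | 0.5 | 4.6% / 4.9% | 80.5% / 81.1% | 0.6 |
| 50% | 0.3 | 4.3% / 5.0% | 81.0% / 82.6% | 1.6 |
| 50% | 0.2 | 3.7% / 4.9% | 82.0% / 84.6% | 2.6 |

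Gains are taken from unrounded power. At an extreme odds ratio of 0.1 the gain is 2.5 points (30% dilated) or 4.6 points (50% dilated). Over odds ratios 0.5 to 0.2, the two tests reach different conclusions in 0.4 to 2.6% of trials under the alternative. Separate simulations of the same design, allowing for simulation error, widen the ranges slightly, to 3.7 to 4.9% for type I error and 0.4 to 2.8 points for power.

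**5. Choosing between the tests.** Rejecting when either test is significant gave type I error of 4.9 to 5.05% in 200,000 simulated null trials per scenario (30, 40 or 50% dilated, duct odds ratio 1 to 0.1). When the duct factor is prognostic, nearly every chi-square rejection is also a rejection by the stratified test.

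**The case against.** The best defence is that the text does rank the tests in part. Superiority is attached only to the chi-square, and the logistic model follows as an adjustment of it. That order is explicit for the secondary endpoints, and 294 per arm is the unadjusted figure. On this reading the general sentence is loosely worded, and labelling the chi-square primary would remove the ambiguity just as well. Details such as the effect measure can also wait for the SAP, which is to be final before database closure.

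Much of this stands. It is fair to read the chi-square as the leading test, and fair to say that it is valid. It does not remove the contradiction: that reading makes the all-tests-adjusted rule untrue, and the primary endpoint lacks the ordering word that the secondary endpoints have. Labelling the chi-square primary would also require withdrawing the general rule and giving up a small free gain.

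A reader might also infer that two tests at 5% in an open-label trial let the false-positive rate rise. The check in step 5 of the working does not support this: with balanced strata the rate stays at about 5%. Imbalance from incomplete blocks was not modelled.

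**Conclusion.** The point holds as an internal contradiction of moderate severity, with a free improvement attached. The protocol's rule and its named superiority test disagree, and the adjusted model has no stated standing.

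The efficiency cost is modest: type I error of about 3.7 to 4.9% and 0.4 to 2.8 points of power, for assumed duct odds ratios of 0.5 to 0.2 with 30 to 50% dilated ducts. It vanishes at an odds ratio of 1. The document supports only the direction of the duct effect. Procedure contributes little, since Table 4 gives 30.3% and 27.3%.

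Two stronger readings are not supported. The sample size is not wrong: 294 and 654 reproduce, and the chi-square kept at least 80% power in every scenario. Nor can a gain much above 3 points be claimed, since that needs a duct odds ratio near 0.1, for which the document offers no evidence.

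**What to change.** In the Statistical Analysis section of the protocol, and in the SAP before outcomes are compared by arm:

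1. Name one stratum-adjusted test as the primary superiority test at two-sided 5%. This can be the logistic model already planned (treatment, procedure, duct dilatation) or a Cochran-Mantel-Haenszel test across the four strata.
2. Report the effect as an adjusted risk difference with a 95% confidence interval, so that it is on the scale of the 30% versus 20% hypothesis. With the logistic model this means averaging predicted risks over the trial population.
3. Label the unadjusted chi-square or Fisher test as supportive.
4. Use the same order for the binary secondary endpoints.

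This brings the section into line with its own general rule. It costs a sentence or two of text. No additional patients or data are needed, and the sample size stays as it is.

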### Study Objectives

The main objective of this study is to compare 90-day ≥grade B or C postoperative pancreatic fistula as defined by the last ISGPF classification between patients who receive perioperative somatostatin and octreotide.

Secondary objectives include the following endpoints between patients who receive perioperative somatostatin and octreotide:

60-day grade 3 pancreatic complication rates (fistula, leak, and abscess) as defined by the Memorial Sloan Kettering Cancer Center surgical secondary events system (Table 1).90-day overall PF rate (grades A, B, and C) as defined by the previous ISGPF classification.90-day overall PF rate (grades B and C) as defined by the last ISGPF classification.90-day overall complication rate (grades 1–5), severe complication rate (grades 3–5), and mortality (grade 5) according to Dindo–Clavien classification [(14) #398] (Table 2).Overall length of drainage required in patients who develop pancreatic complications—overall length of stay and readmission rate.Cost-effectiveness.Postoperative quality of life after pancreatic surgery (only in patients undergoing PD).

**Table 1 T1:** Memorial sloan kettering cancer surgical secondary events database classifications.

**Grade**	**Surgical secondary event requiring or resulting in**
Grade 1	Bedside care or oral medications
Grade 2	Intravenous medications, transfusion
Grade 3	Radiologic, endoscopic, or operative intervention required
Grade 4	Chronic disability or organ resection
Grade 5	Death

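### The 60-day pancreatic complication endpoint is written as grade 3 alone; read literally, it can leave out pancreatic complications graded 4 or 5

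*Protocol article*

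**What the plan says.** In the protocol article, Study Objectives lists among the secondary endpoints "60-day grade 3 pancreatic complication rates (fistula, leak, and abscess) as defined by the Memorial Sloan Kettering Cancer Center surgical secondary events system". Statistical Analysis repeats it as "The 60-day grade 3 pancreatic complication rate (fistula, leak, and abscess") and compares the arms by χ² or Fisher's exact test, then by logistic regression adjusted for the stratification variables.

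The scale is Table 1, headed "Surgical secondary event requiring or resulting in". Its upper rows are:

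- grade 3: "Radiologic, endoscopic, or operative intervention required"
- grade 4: "Chronic disability or organ resection"
- grade 5: death

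For the other scale, Dindo–Clavien, the same sentence of Statistical Analysis gives a range: "as well as the severe complication rate (grades 3–5"). Study Objectives does the same.

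**The concern.** Neither statement of the 60-day endpoint has a ≥ sign, a range or words such as *or higher*. The article does spell out a range for Dindo–Clavien in the same list and the same sentence. A programmer working from this text would therefore have good reason to code grade equal to 3.

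The Introduction says that a fistula can lead to reoperation, intensive care or death, so pancreatic complications above grade 3 are foreseeable. If they drop out, the endpoint no longer rises steadily with severity: a complication that worsens from grade 3 to grade 4 or 5 can move from counted to not counted. The rate would be too low in both arms, and any imbalance in the worst outcomes would work in favour of the arm that had more of them.

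**Working it through.** **1. The plan's own figures.** The article gives no expected rate, difference or power for the 60-day endpoint. Its only sample size is for the primary endpoint (Sample Size Considerations: 30% versus 20%, two-sided 5%, 80% power):

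n = [1.960·√(2·0.25·0.75) + 0.842·√(0.30·0.70 + 0.20·0.80)]² / 0.10² = 293.2, so 294 per arm

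2 × 294 = 588, and 588 / 0.90 = 653.3, so 654 in total

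Both printed figures reproduce. This point does not touch them.

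**2. Wording against scale.**

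| Place | What is printed |
|---|---|
| Study Objectives, 60-day endpoint | grade 3, no sign or range |
| Statistical Analysis, 60-day endpoint | grade 3, no sign or range |
| Table 1 | grades 3, 4 and 5 as separate rows |
| Study Objectives and Statistical Analysis, severe Dindo–Clavien complications | grades 3–5 |

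Nothing in the article adds grades 4 and 5 to the 60-day endpoint.

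**3. Effect on the comparison.** Assume each patient is classified by the worst pancreatic complication grade. Let p be the proportion at grade 3 or higher and g the proportion at grade 4 or 5, with C for control and E for experimental. The grade-3-only rate is p − g, so

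difference shown (C − E) = (p_C − p_E) + (g_E − g_C)

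The error is g_E − g_C. It is zero when grades 4–5 are balanced. Otherwise it favours the arm with more of them.

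**4. Illustration.** All rates below are assumptions.

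| Grade 3 or higher, C vs E | Grades 4–5, C vs E | True difference | Grade 3 only, C vs E | Difference shown |
|---|---|---|---|---|
| 20% vs 20% | 2% vs 2% | 0 | 18% vs 18% | 0 |
| 20% vs 20% | 2% vs 4% | 0 | 18% vs 16% | 2 points for E |
| 20% vs 20% | 1% vs 5% | 0 | 19% vs 15% | 4 points for E |
| 20% vs 20% | 4% vs 2% | 0 | 16% vs 18% | 2 points for C |
| 20% vs 12% | 2% vs 2% | 8 | 18% vs 10% | 8 points for E |
| 20% vs 12% | 4% vs 2% | 8 | 16% vs 10% | 6 points for E |

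**5. Effect on the test**, with 294 per arm, two-sided 5% and p̄ the mean of the two rates:

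power = Φ{[|p_C − p_E|·√294 − 1.960·√(2·p̄·(1 − p̄))] / √[p_C(1 − p_C) + p_E(1 − p_E)]}

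- Last row, 20% vs 12%: Φ[(1.372 − 1.016)/0.515] = 75.5%. As 16% vs 10%: Φ[(1.029 − 0.932)/0.474] = 58.1%. A real benefit that includes fewer of the worst outcomes becomes harder to show.
- Second row, 18% vs 16%: Φ[(0.343 − 1.041)/0.531] = 9.4%. This is the chance of a nominally significant result in favour of E, against 2.5% if the rates were equal.

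**The case against.** **The counting rule is not stated.** The article nowhere says that a complication carries only its highest grade. Assessment of Efficacy describes percutaneous or operative drainage as the treatment of fistula, leak and abscess alike. A patient drained for a leak who later dies has had a complication that required intervention and might still count as grade 3. This stands: exclusion is a conditional reading. Table 1 points towards it, because its heading grades an event by what it requires or results in, but does not settle it. The gap is itself a reason to state a rule.

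**A sign may have been lost.** Study Objectives prints "compare 90-day ≥grade B or C postoperative pancreatic fistula" where Statistical Analysis prints "90-day = grade B or C postoperative pancreatic fistula", so the article is not reliable on this symbol. That weakens any inference that grades 4–5 were excluded on purpose. But the 60-day endpoint carries no sign in either place, so the text needs correcting whichever was meant.

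**Other endpoints catch the worst outcomes.** The 90-day severe complication rate (grades 3–5) and 90-day mortality are compared between arms and reappear in the economic evaluation. An arm with more deaths would be visible there. This stands as a partial offset. Those endpoints are all-cause, on another scale and over another period, and do not repair the 60-day pancreatic rate.

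**A stronger reading to avoid.** From the 2–4% mortality in the Discussion a reader might infer 654 × 0.02 = 13 to 654 × 0.04 = 26 deaths, attribute half to pancreatic complications (7 to 13), and argue that an imbalance of 10 patients shifts the rate by 10/327 = 3.1 points. The article does not support this. The half is a guess, the mortality is a background figure, and 654 includes patients expected not to be resected. With 7 such deaths in both arms together, an imbalance of 10 is impossible. With 13 it needs a 12–1 or 13–0 split, which has probability 28/8192 = 0.3% if the arms are alike. Grade 4 events would add to the count, but the article gives no number for them.

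**Conclusion.** The concern holds in a limited form. As printed, the 60-day endpoint is grade 3 alone on a scale with two higher grades. If each complication carries its highest grade, pancreatic complications graded 4 or 5 go uncounted, the rate is understated, and any imbalance in them biases the comparison towards the arm with the worse outcomes.

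The size cannot be fixed from the article. Under the assumed rates above, the error runs from none (balanced) to 2 points (2% versus 4%) or 4 points (1% versus 5%).

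A reader might infer that every patient whose fistula ends in death or organ resection is scored as a success, or that the plan deliberately leaves such patients out. The article establishes neither. Nor does the endpoint's place at the head of the secondary list give it rank, since no hierarchy is stated. The primary endpoint and the sample size are unaffected.

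**What to change.** In both Study Objectives and Statistical Analysis, replace grade 3 with *grade 3 or higher (grades 3–5)* for the 60-day pancreatic complication endpoint. Add one sentence: each patient counts once, by the worst grade of pancreatic complication (fistula, leak or abscess) up to day 60.

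The cost is a few words in two places and one sentence on counting. No new data are needed, and the sample size and primary analysis stay as they are. The change should be made before the database is closed and carried into the statistical analysis plan.

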### Assessment of Efficacy

The primary efficacy endpoint is a decrease 90 days grade B or C postoperative PF as defined by the last ISGPF classification between patients who receive perioperative somatostatin and octreotide. The definitions of the grade B or C postoperative PF to be used in this study are provided previously. Clinical examination is performed every day to collect manifestations related to PF and its complications. Clinical examination includes temperature, sign of sepsis or infection, and drainage output. Biological evaluation, i.e., amylase dose at 6:00 a.m. on the 24 h drain fluid and blood, is performed on postoperative days 1, 3, 5, and 7 to collect manifestations related to PF. Imaging requested by the clinical manifestation is recorded. Need for reoperation, radiological drainage, and readmission are recorded. Assessment for pancreatic and non-pancreatic complications is made at the time of discharge and in follow-up by the attending surgeon. Pancreatic complications are defined as PF, leak, and abscess. These three complications are typically grouped together because their definitions overlap, the mechanism by which they occur is presumed to be similar (leakage of pancreatic exocrine secretion and/or enteric contents), the presentation is similar (elevated drain output if drain in place or fever/elevated white blood count if no drain in place), and the treatment is the same (percutaneous or operative drainage). When a pancreatic complication has been identified, study drug (somatostatin) or control treatment (octreotide) will be continued until postoperative day 7 and then discontinued. Management of PF is left at each attending surgeon's discretion.

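### Drainage duration is tested only among patients who develop a pancreatic complication, a group formed after randomization that includes the outcome under treatment, so the comparison is not randomized and may be biased in either direction

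*Protocol article*

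**What the plan says.** Study Objectives lists as a secondary endpoint "Overall length of drainage required in patients who develop pancreatic complications". Statistical Analysis turns it into a formal between-arm test: "The overall duration of drainage required in patients who develop pancreatic complications and the overall length of stay will be compared" by Student's t test, or by a Wilcoxon test if the data are not normal. Linear regression then adjusts for the stratification variables, which are type of procedure and main-duct dilatation.

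The event that defines the group is given in Assessment of Efficacy: "Pancreatic complications are defined as PF, leak, and abscess". Randomization takes place "in the operating room just after skin incision and surgical exploration to exclude patients with carcinomatosis and metastasis", so it precedes every such event. The same event is the drug's target. Assessment of Efficacy states "The primary efficacy endpoint is a decrease 90 days grade B or C postoperative PF", and Sample Size Considerations puts the grade B/C rate at about 30% and hypothesizes 20% under somatostatin.

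Statistical Analysis assigns secondary analyses to the intention-to-treat and per-protocol populations. The article describes no comparison of drainage over all randomized patients.

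**The concern.** Randomization makes the arms comparable at the time of assignment. It does not make the patients who later have a complication comparable. If somatostatin prevents some complications, those that remain under somatostatin are a differently selected set from those under octreotide. A difference in mean drainage between the sets then mixes two things: any effect on how long a given complication needs drainage, and the change in which complications occur.

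The planned adjustment does not separate them. Procedure and duct diameter are baseline variables, and neither measures the severity of the complications that remain.

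At stake is the reading of one secondary endpoint. A drug that works could appear to prolong drainage, appear to do nothing, or appear to shorten it, depending on which complications it prevents.

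**Working it through.** **The plan's own figures.** With p1 = 0.30, p2 = 0.20, pooled p = 0.25, two-sided alpha 0.05 and power 80%:

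n = [1.96·√(2·0.25·0.75) + 0.8416·√(0.30·0.70 + 0.20·0.80)]² / 0.10² = (1.2002 + 0.5119)² / 0.01 ≈ 293.1, rounded up to 294 per arm.

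Inflation: 588 / 0.90 = 653.3, rounded up to 654. Both stated figures reproduce. The concern does not depend on them, but they give the size of the groups compared.

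**Size of the restricted groups.** Using the grade B/C rate as a stand-in for the pancreatic-complication rate: 294 × 0.30 ≈ 88 control patients against 294 × 0.20 ≈ 59 somatostatin patients.

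**Illustration.** The article gives no drainage durations, so these inputs are assumptions:
- complications in 30% (control) and 20% (somatostatin);
- control complications split evenly, 15% mild and 15% severe;
- 10 drain days if mild, 20 if severe;
- treatment changes which complications occur, not how long a given type is drained.

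Restricted mean = (%mild × 10 + %severe × 20) / (%mild + %severe).
All-patient mean of complication-related days = (%mild × 10 + %severe × 20) / 100.

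Control: restricted 450/30 = 15.0 days; all patients 450/100 = 4.5 days.

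| Complications prevented | Somatostatin mild / severe | Restricted mean | Difference from 15.0 | All-patient mean | Difference from 4.5 |
|---|---|---|---|---|---|
| Only mild | 5% / 15% | 350/20 = 17.5 | +2.5 | 3.5 | -1.0 |
| Proportional | 10% / 10% | 300/20 = 15.0 | 0 | 3.0 | -1.5 |
| Only severe | 15% / 5% | 250/20 = 12.5 | -2.5 | 2.5 | -2.0 |

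**If routine drains count.** Giving every uncomplicated patient 5 drain days adds 0.70 × 5 = 3.5 to control and 0.80 × 5 = 4.0 to somatostatin. The all-patient means become 8.0 against 7.5, 7.0 and 6.5, so the differences are -0.5, -1.0 and -1.5 days.

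**Range.** With severe drainage of 30 days, the restricted control mean is 600/30 = 20.0 and the somatostatin means are 25.0, 20.0 and 15.0. The restricted differences are +5, 0 and -5 days. The all-patient differences are -1.0, -2.0 and -3.0 (uncomplicated counted as 0), or -0.5, -1.5 and -2.5 (uncomplicated counted as 5).

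**Chance of a misleading test.** Assume an SD of 10 days. SE = 10·√(1/88.2 + 1/58.8) = 1.68 days. When only mild cases are prevented, the probability of a significant result against the effective drug is Φ(2.5/1.68 - 1.96) ≈ 32%, and Φ(5/1.68 - 1.96) ≈ 84% with 30-day severe cases.

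**Adjustment.** Suppose the first row of the table holds within each stratum of procedure and duct dilatation. The stratum-specific differences are then all +2.5 days, and the adjusted coefficient is also +2.5 days.

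**The case against.** The strongest points on the other side are these.

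- *The 30% and 20% rates are for grade B/C fistula, not for the restricted group.* This stands. Fistula, leak and abscess together are broader: Table 4 gives all-grade fistula rates of 34.2% and 55.6% beside B/C rates of 30.3% and 27.3%, and the Discussion reports these complications in 20–50% of patients. The article states no expected change for the broader group. The rates above are therefore a stand-in. The argument needs only that the group contains the target outcome, which it does.
- *Durations and severity split are invented.* This also stands, and it is why a range is shown. A reader might infer that the plan is biased against somatostatin. The documents do not support that, because nothing in them says which complications would be prevented.
- *An all-patient measure answers a different question.* True. It combines how often drainage is needed with how long it lasts. It is, however, a comparison that randomization supports.
- *Readers will see the complication rates alongside.* The comparisons of fistula, complications, mortality, readmission and stay are not restricted in this way, which limits the harm. It does not make the drainage test valid.

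A reader might also infer that length of stay, named in the same sentence, is faulty because death shortens it. The article does not restrict stay to complicated patients and says nothing on deaths. How deaths are handled is detail commonly left to the SAP, so no fault is shown there.

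**Conclusion.** The concern holds for the drainage test. Both the restriction and the between-arm test are written into the article, so this is a choice the plan makes and not a detail left open. The test compares groups selected by a post-randomization event that treatment is meant to change, and the planned adjustment does not repair this.

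The size cannot be fixed from the documents. Under the stated assumptions the restricted difference for an effective drug runs from +2.5 to -2.5 days, or from +5 to -5 with longer severe drainage. The all-patient difference favours the drug in every case. That last result follows from the assumptions that the drug only prevents complications and that an uncomplicated patient is drained for less time than a complicated one.

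The point concerns one secondary endpoint. It should be corrected, but the primary intention-to-treat analysis of grade B/C fistula is not affected.

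**What to change.** In the SAP, which the article says will be finalized before database closure, and in the protocol wording:

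1. Make the tested comparison drainage days to day 90 in all randomized patients, the intention-to-treat set already named for secondary analyses. Count complication-related drainage as 0 for patients without a pancreatic complication.
2. State a rule for deaths, so that dying early is not scored as short drainage.
3. Report duration among patients with complications by arm descriptively, without a test.

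The population should not be narrowed to resected patients. Randomization precedes resection and Sample Size Considerations expects 10–20% not to be resected, so that would again select on a post-randomization event.

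**Cost.** If only complication-related drainage is counted, the change is one of wording, because durations in complicated patients are already needed for the planned endpoint and everyone else scores 0. If routine surgical drains are to count, removal dates are needed for all patients; the article describes drain output and amylase but not removal dates, so collection would have to be checked. The new measure also combines frequency and duration. With roughly 70–80% zeros under the stand-in rates, a rank test would mainly reflect frequency. A mean difference with a bootstrap interval, a technique already planned for costs, would be easier to interpret.
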